#### Data analysis

3.7.2

Data will be statistically analyzed using PASW Statistics 18.0, STATA 14.0 and R 4.3.0. Continuous variables will be summarized as means with standard deviations or medians with interquartile ranges, whereas categorical variables will be presented as counts and percentages. The primary outcome will be outlined using descriptive statistics. Building on reported positive associations between colder temperatures, male sex, and more consultations for musculoskeletal pain (76), we will conduct subgroup analyses to explore how season and sex influence enrolment, retention, and adherence, thereby informing weather-adaptive management strategies for the future full RCT. Secondary outcome measures will be analyzed based on the intention-to-treat population approach. Any post-randomization participants who received at least one intervention session will be included in the full analysis set. Among these, those who completed at least 80% of the planned treatments without any significant protocol violations will be categorized into the per-protocol analysis set. Any post-randomization participants receiving at least one intervention session will be classified into the safety analysis set. Any missing data will primarily be handled using multiple imputation, with last observation carried forward applied for sensitivity analysis.

We will analyze both within- and between-group changes for each efficacy-related secondary outcome variable using a linear mixed-effects model to derive estimates of intervention effects.

Group allocation, time-point and the interaction between group allocation and time-point will act as fixed-effects, individuals as random effects, and baseline measurements as covariates. Given that this exploratory trial is not formally powered to assess effects, a recommended confidence interval of 75% will be employed to infer the size and direction of the calculated effect estimates (77). The 75% confidence interval will be compared with the MCIDs to preliminarily assess whether the difference between treatment groups holds potential for clinical significance (77). The remaining secondary outcome measures involving AER, ARR, and intervention costs, as well as baseline variables, will be presented descriptively by the groups.

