## Introduction

1

Cervical radiculopathy (CR) is a term used to describe a consequence triggered by mechanical compression of nerve roots within the neural foramen due to age-related degenerative changes in the cervical spine, i.e., herniated disk material, hypertrophied facet joints, and/or uncovertebral joints (1–5). It is a prevalent, debilitating cervical spine condition characterized by pain in the cervicobrachial region and abnormal neurologic signs along the path of innervation of the affected nerve root, including paraesthesia, numbness, muscle weakness and diminished deep tendon reflexes. The annual incidence has been reported to be between 0.83 and 1.79 per 1,000 person-years, with an estimated prevalence from 1.21 to 5.8 per 1,000 (6). CR is frequently described as a self-limiting disorder with a favorable prognosis (7, 8). However, pain during the first weeks to months is often excruciating (9), and most patients report experienced continuous, fluctuating pain for up to 24–36 months before achieving complete recovery (10, 11). Such pain contributes to impaired physical function, poor mental well-being, limited regular activities, and isolated social life (12–14). It has been reported that approximately 352.0 cases per 100,000 individuals worldwide have suffered from disability resulting from CR over the past three decades (15). Patients with CR are vulnerable to experiencing varying degrees of work ability impairment due to both physiological disturbances and psychological distress (13, 14, 16). Hence, they may be at a higher risk of exclusion from the labor market due to frequent sick leave, work absenteeism, and even failure to execute work duties (13, 14). Patients with CR are also believed to experience poorer economic outcomes as a result of work productivity loss, with an estimated average willingness-to-pay far exceeding $38.0 per month for a 1-point reduction in pain (17).

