#### Prohibited therapies

3.5.3

Any therapies that might alleviate cervicobrachial pain beyond usual care will be prohibited during study participation, including dehydrating agents, neurotrophic drugs, skeletal muscle relaxants, Chinese herbal medicine, acupuncture, cupping, physical therapy and exercise therapy. Participants who consider pain reduction to be insufficient may seek alternative therapeutic options, but will be withdrawn from the trial.

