The TMG assumes responsibility for day-to-day trial operations. It will consist of a project manager, a registered research physician, a registered therapist, a trial coordinator, two research assistants and a data manager. All members will attend a pre-trial training workshop to familiarize themselves with the trial implementation process, and to ensure adherence to the study protocol and standard operating procedures. The trial coordinator is to formulate follow-up programs based on the study protocol. They will keep in touch with participants to facilitate their attendance at scheduled follow-ups, but also to assist in promptly detecting any AE. The research assistants will collect and record data on paper case report forms (CRF), including participants’ socio-demographics (age, sex, education level, employment status, health insurance, etc.), medical history (comorbidities, concomitant medications, details related to the cervicobrachial pain episode, etc.) and physical examination at baseline (dominant hand, abnormal deep tendon reflexes, radiculopathy level shown on magnetic resonance imaging, etc.) and discharge (abnormal deep tendon reflexes), secondary outcomes, treatment information, and adverse event details. Data may be collected within 1 day after the scheduled time. Unless they explicitly refuse, research assistants will follow up with any withdrawn participants to acquire data until the trial end. Additionally, they will track any AE from reporting until resolution. The data manager will regularly monitor data quality, working with research assistants to recover missing data and clarify ambiguous data to ensure all reported data are accurate, complete, legible and verifiable from source documents. Research assistants will double-enter the data from the paper CRF after monitoring into an Epidata-based electronic data capture system. Any discrepancies from double entry will be verified against the paper CRF. The data manager will lock the electronic data capture after all data have been cleaned; researchers will be unable to modify the data. The TMG will meet weekly to review study progress during the trial. The project manager will meet with the TSC biweekly to align on key decisions.

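### The intention-to-treat label does not match a full analysis set limited to treated participants, and LOCF is a weak sensitivity check that misleads when missingness differs between arms

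*Protocol article*

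**What the plan says.** Section 3.7.2 (Data analysis) states the principle: "Secondary outcome measures will be analyzed based on the intention-to-treat population approach". The next sentence sets the population: "Any post-randomization participants who received at least one intervention session will be included in the full analysis set". The per-protocol set is a subset of that one. The safety set uses the same entry rule: "Any post-randomization participants receiving at least one intervention session will be classified into the safety analysis set".

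On missing values, the same section says: "Any missing data will primarily be handled using multiple imputation, with last observation carried forward applied for sensitivity analysis". The article names no other sensitivity analysis.

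Three other places bear on this:

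- Section 3.5.3 (Prohibited therapies): "Participants who consider pain reduction to be insufficient may seek alternative therapeutic options, but will be withdrawn from the trial".
- Section 3.8 (Trial management and quality control): "Unless they explicitly refuse, research assistants will follow up with any withdrawn participants to acquire data until the trial end".
- Section 1 (Introduction): "CR is frequently described as a self-limiting disorder with a favorable prognosis".

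Section 3.4 says that participants and treatment providers cannot be blinded.

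**The concern.** There are two linked problems in the stated rules.

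First, intention-to-treat means everyone randomised, analysed as allocated. The only full efficacy set in the article adds a condition that arises after randomisation. Participants learn their allocation, so a person disappointed by it can leave before the first prescription or AMT session. Exclusion could then differ by arm for reasons related to outcome.

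Second, a sensitivity analysis should show how far the main result depends on the assumption behind it. Multiple imputation normally rests on missing at random. LOCF does not relax that assumption in a controlled way; it substitutes the claim that nothing changes after the last visit. If pain is falling in everyone, LOCF holds the missing at an earlier, worse score, so the arm with more missing data looks worse. It also treats filled-in values as if they had been observed.

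At stake is the efficacy signal. Section 3.7.2 compares 75% intervals with minimum important differences, section 5 says the analytic strategy gives unbiased estimates for later power calculation, and the abstract lists better health outcomes with AMT among the pilot's success targets.

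**Working it through.** The plan gives no figure to reproduce here. The check is a comparison of the text, plus illustrations in which the pain course, the missing-data rates and the SD are assumed, because the article gives none of them.

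**Analysis sets side by side**

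| Set | Entry rule in section 3.7.2 |
|---|---|
| Stated principle | intention-to-treat |
| Full analysis set | randomised, with at least one session |
| Per-protocol set | subset of the above: 80% of treatment, no major violation |
| Safety set | same rule as the full analysis set |

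No row contains all 48 randomised participants. Taking the full analysis set as the intention-to-treat population is an inference from adjacent sentences, but the article offers no other candidate.

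**Possible shift from excluding non-starters.** The arm size of 24 is from section 3.1. If x participants in one arm are excluded and their outcomes differ by D points (assumed), the arm mean moves by (x/24) × D:

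- x = 1, D = 1: 1/24 × 1 = 0.04
- x = 2, D = 2: 2/24 × 2 = 0.17
- x = 3, D = 3: 3/24 × 3 = 0.38

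**LOCF, simple formula.** Let R be the average improvement still to come when data stop, and m the proportion missing. LOCF overstates final pain in an arm by m × R. With no true effect, the bias in AMT minus usual care is (m_AMT − m_UC) × R; negative favours AMT.

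| Missing, usual care / AMT | R = 1 | R = 2 | R = 3 |
|---|---|---|---|
| 20% / 20% | 0 | 0 | 0 |
| 25% / 15% | −0.1 | −0.2 | −0.3 |
| 30% / 10% | −0.2 | −0.4 | −0.6 |
| 10% / 30% | +0.2 | +0.4 | +0.6 |

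For scale, section 4 sets retention targets of at least 80%, with possible infeasibility below 70%.

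**LOCF, two simulations, no true effect.** Simulation A: 200,000 per arm; mean pain 6.5, 5.5, 4.8, 4.3, 4.0 over five visits; between- and within-person SD 1.2; loss more likely with higher pain. Simulation B: 400,000 in total; mean baseline about 6; mean improvement 3 points over four periods; loss possible once observed relief is under 10%. Both treat everyone who leaves as missing.

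| Simulation | Missing, usual care / AMT | LOCF difference |
|---|---|---|
| A | 20% / 5% | −0.21 |
| A | 30% / 10% | −0.27 |
| A | 10% / 25% | +0.21 |
| A | 20% / 20% | +0.01 |
| B | 33% / 11% | −0.45 |
| B | 11% / 33% | +0.44 |
| B | 21% / 22% | 0.00 |

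In simulation B the full-data difference was within 0.01 of zero in all three rows, and imputation under missing at random stayed within 0.01 of the full-data value. With a true effect of −1, LOCF gave −1.45 (33% / 7% missing), −0.59 (12% / 23%) and −1.02 (21% / 14%).

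**Scale.** With SD 2 (assumed) and 24 per arm, the 75% interval half-width is 1.15 × 2 × √(2/24) = 0.66 (0.67 with a t quantile). A bias of 0.21 to 0.45 is about a third to two thirds of that, and 10% to 23% of the 2-point NRS benchmark in section 3.6.2.

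**Within-arm change.** Equal missingness protects the contrast but not the planned within-group analysis. At 20% missing and R of 1 to 3, final pain is overstated by 0.2 to 0.6 points in each arm.

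**The case against.** The strongest reply is that withdrawal is not the same as missing data. Section 3.8 has withdrawn participants followed to the end of the trial unless they refuse, so LOCF touches only those who refuse or cannot be reached. That stands: the percentages in the illustrations are missing-data rates, and true rates may be well below the withdrawal rates.

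Second, multiple imputation is the main method. A reader might infer that the withdrawal rule in section 3.5.3 makes the main estimate biased. The documents do not support that. Pain is scored at each period's first visit, and loss that depends on recorded pain is compatible with missing at random; imputation recovered the full-data contrast in simulation B. That simulation was built with loss depending on observed relief, so it does not rule out other mechanisms, but nothing in the article establishes one.

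Third, a reader might infer that LOCF is biased between arms whenever pain improves and poor responders leave. It is not: both equal-missingness runs gave differences of 0.01 or less. Unequal missingness is also needed, and the article neither states nor predicts it. The introduction also describes pain lasting up to 24 to 36 months, so improvement over four weeks may be modest.

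Fourth, baseline is taken at the first visit after randomisation, just before treatment, and both arms get usual care. The window for leaving untreated is short, and the number affected may be zero.

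Finally, a fuller analysis plan may contain more sensitivity analyses. What remains is that the rules the article does state are the wrong ones for the stated purpose.

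**Conclusion.** The point holds in a limited form. The stated principle and the stated analysis set disagree, and no set of all randomised participants is defined. The numerical effect is probably small: 0.04 to 0.38 NRS points on one arm's mean if 1 to 3 of 24 are excluded and differ by 1 to 3 points.

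LOCF is a poor sensitivity analysis here because it does not examine the assumption behind the multiple imputation. When missingness differs by 15 to 22 percentage points, it moves the contrast by about 0.2 to 0.45 points, in either direction depending on which arm loses more; when missingness is equal, the shift is near zero. A disagreement between LOCF and multiple imputation could therefore reflect unequal loss alone, and agreement would say little about robustness. All these sizes rest on assumed trajectories and missing-data rates.

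A reader might go further and conclude that the feasibility decision is compromised. It is not: the enrolment, adherence and retention thresholds in section 4 do not depend on LOCF or on the full analysis set, and the feasibility outcomes are descriptive. The affected outcomes are secondary and exploratory, so severity is low to moderate.

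**What to change.** Three changes to section 3.7.2:

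1. Define the full analysis set as all randomised participants, analysed as allocated. State that outcome data collected after treatment stopped or changed are used; section 3.8 already plans to collect them.
2. Keep the one-session rule for the safety set only. The per-protocol set needs no change, since its 80% completion rule already implies treatment.
3. Replace LOCF with a delta-adjusted analysis built on the planned multiple imputation. For participants who left for insufficient relief and have no later data, worsen the imputed NRS scores over a range fixed in advance, for example 0.5, 1, 1.5 and 2 points (the top value matching the section 3.6.2 benchmark). Report where, if anywhere, the conclusion changes. Scale the range similarly for the other measures.

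The cost is wording and a little extra analysis; no sample size or data collection changes. There are two downsides. A few participants may contribute only imputed follow-up. Data recorded after a switch to other therapy will also reflect that therapy, so the article should say plainly that the comparison is of allocated strategies.

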## Objectives

2

The aim of this external pilot study is to ascertain the feasibility of a definitive full-scale RCT that determines whether AMT plus usual care is superior to usual care alone in clinical efficacy and cost-effectiveness regarding cervicobrachialgia reduction. In this study, we will (1) evaluate the recruitment and retention of participants, treatment adherence, and completion of proposed outcome measures to inform the feasibility and acceptability of study design; (2) and estimate the variability of efficacy-related outcomes to preliminarily inform sample size calculation for a future fully powered RCT.

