### Randomization and blinding

3.4

Eligible participants will be assigned to either the experimental group (AMT add-on) or the control group (usual care alone) at a 1:1 ratio with a random allocation schedule, which will be generated by a third-party biostatistician using R software (version 4.3.0). The treatment allocation table will be stratified by baseline cervicobrachial pain level (NRS < 7 or ≥ 7) and sex, then randomized with varying block sizes to avoid insufficient concealment caused by limited sample size. The random allocation schedule will be concealed in sequentially numbered, sealed, opaque envelopes, and managed by the biostatistician. He will reveal the treatment allocation via phone according to the participants’ enrolment sequences.

Due to the nature of the intervention, it will be impossible to blind the participants and treatment providers. However, outcome assessors, data managers and statistical analysts will be unaware of the treatment allocations.

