#### Sample size

3.7.1

The primary objective of the pAMTLER is to determine the feasibility of a future definitive full-scale RCT based on recruitment rate, retention rate, and intervention acceptability. With pre-specified feasibility thresholds of ≥25% recruitment, ≥80% retention and ≥80% adherence, at least 48 eligible participants are required to have a 95% confidence interval with a maximum width of 20% (75). This sample size, in a resource-limited setting, is considered adequate to provide a reasonable estimate of outcome variability across the four strata (12 participants per stratum), defined by sex and baseline cervicobrachial pain level (75).

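### The efficacy mixed model names neither randomisation stratification factor; if these are prognostic beyond baseline, the 75% intervals will be somewhat too wide

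*Protocol article*

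**What the plan says.** Section 3.4 (Randomization and blinding) says that allocation is "stratified by baseline cervicobrachial pain level (NRS < 7 or ≥ 7) and sex, then randomized with varying block sizes", which gives four strata.

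Section 3.7.2 (Data analysis) sets out the efficacy model term by term: "Group allocation, time-point and the interaction between group allocation and time-point will act as fixed-effects", with "individuals as random effects, and baseline measurements as covariates". No term for sex or for the pain stratum appears.

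The same section says that "a recommended confidence interval of 75% will be employed to infer the size and direction of the calculated effect estimates", and then "The 75% confidence interval will be compared with the MCIDs to preliminarily assess" whether the group difference could be clinically relevant.

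The second objective in section 2 is to "estimate the variability of efficacy-related outcomes to preliminarily inform sample size calculation for a future fully powered RCT". Nothing says whether that variability is a raw SD or a model residual SD.

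**The concern.** Stratified randomisation forces the arms to be nearly balanced on the stratification factors, which removes their contribution from the sampling variation of the treatment difference. The reported standard error reflects that gain only if the factors are also in the model. If they are left out and are prognostic, their variance stays in the residual. The standard error is then larger than the true sampling error, and an interval labelled 75% covers more than 75% of the time.

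Two things in the plan depend on this: the comparison of the 75% intervals with the MCIDs, and possibly the SD used to size the definitive trial. Section 3.7.1 also defends the sample size partly by how well variability can be estimated across the four strata, which sits awkwardly with an efficacy model that does not use them.

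**Working it through.** **Which factors are missing, and for which outcomes.** The model's baseline covariate is not defined. Three features of the text favour the narrow reading, the baseline value of the outcome being analysed:
- Section 3.7.2 separately refers to baseline variables as something to be summarised descriptively by group.
- The headings of sections 3.6.1 and 3.6.2 use the word measurements for outcomes.
- The baseline assessment in Figure 1 lists sex under socio-demographics.

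On that reading:

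| Outcome | Sex in model? | Baseline pain in model? |
|---|---|---|
| Cervicobrachial pain NRS | No | Yes, as the continuous NRS behind the cut at 7 |
| All other efficacy outcomes (e.g. NDI, QuickDASH, grip strength, WPAI, EQ-5D-5L, SDS, SAS) | No | No |

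**Inputs.** From the documents: N = 48, 1:1 allocation, four strata, 75% two-sided intervals. Assumed, because the documents give no figure: the share R² of residual variance that the omitted factor explains after the outcome's own baseline. The plan states no interval width or SD for this model, so there is no figure of its own to reproduce.

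**Analytic check.** Take one time-point with complete data. The model with group and baseline has 48 − 3 = 45 residual degrees of freedom; adding one factor leaves 44. The ratio of interval width, factor omitted to factor included, is

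t(0.875, 45) / [t(0.875, 44) × √(1 − R²)],

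with t(0.875, 45) = 1.1654 and t(0.875, 44) = 1.1657. The residual SD ratio is 1/√(1 − R²), and the ratio of implied sample sizes is 1/(1 − R²).

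| Assumed R² | Width ratio | SD ratio | Sample-size ratio |
|---|---|---|---|
| 0% | 1.000 | 1.000 | 1.00 |
| 2% | 1.010 | 1.010 | 1.02 |
| 5% | 1.026 | 1.026 | 1.05 |
| 10% | 1.054 | 1.054 | 1.11 |
| 20% | 1.118 | 1.118 | 1.25 |

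**Simulation check.** This used stratified permuted blocks of 2 and 4 (the article gives no block sizes, so these are assumed), N = 48, ANCOVA at one time-point, an assumed residual SD of 1.8, and 4,000 trials per setting. A balanced binary factor with effect d adds d²/4 to the residual variance, so sex effects of 0.5, 1.0 and 1.5 points correspond to R² = (d²/4)/(1.8² + d²/4) = 1.9%, 7.2% and 14.8%. The table gives the width under the stated model divided by the width with sex and pain stratum added:

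| Sex effect | Pain NRS outcome | Outcome partly correlated with pain |
|---|---|---|
| 0 | 0.99 | 1.00 |
| 0.5 | 1.00 | 1.01 |
| 1.0 | 1.03 | 1.04 |
| 1.5 | 1.08 | 1.09 |

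Under the stated model, the nominal 75% interval covered between 74% and 79%. For the pain outcome the empirical SD of the treatment estimate was about 0.52 to 0.53 under either model. The estimate itself is therefore no less precise; only its reported uncertainty grows.

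**Pain stratum in the pain model.** With continuous baseline NRS already fitted, adding the dichotomised stratum gained nothing and widened the interval by about 1% (mean width 1.222 against 1.212 with sex alone, at zero sex effect).

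**The case against.** The strongest reply has four parts.

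*The covariate phrase is undefined and plural, and sex is part of the baseline assessment, so the factors may be covered already; the full specification may sit in an analysis plan that is not shown.* The wider reading is possible, so it cannot be asserted as certain that sex is absent. But the article lists the model's terms, and the narrow reading fits its wording better. Where a design is stratified and the stated model names neither factor, a one-sentence correction is reasonable.

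*The effect is conditional and small.* This stands. A reader might infer that the omission does make the 75% intervals too wide. The documents give no prognostic strength for either factor, and the excess may be zero. The outcome's own baseline will also absorb part of any difference by sex or pain level.

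*The SD is not shown to be affected.* This stands too. A reader might infer that the pilot will pass an upwardly biased SD to the definitive trial. The article never says that this model's residual SD is carried forward. An SD not adjusted for sex is also the correct input for a definitive analysis that does not adjust for sex; for one that does, it is conservative rather than biased.

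*No decision turns on it.* Section 4 bases pilot success and possible infeasibility on enrolment, adherence and retention. Efficacy is secondary, and section 3.7.2 says the trial is not powered for effects. This lowers the severity but does not remove the mismatch between the design and the model.

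A reader might also take the pain stratum to be missing from every model. For cervicobrachial pain itself that does not hold, because the continuous baseline NRS carries the same information.

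**Conclusion.** The concern holds in a limited, conditional form. On the natural reading of section 3.7.2, sex is in no efficacy model, and baseline cervicobrachial pain is absent from the models for other outcomes, although randomisation is stratified on both. If either is prognostic beyond the outcome's own baseline, the 75% intervals set against the MCIDs are conservative: about 1% to 5% too wide for partial R² of 2% to 10%, and about 12% at 20%, which is an upper case. If neither is prognostic, omission costs nothing. The treatment estimate is not biased. The figures assume complete data at a single time-point and a prognostic strength that the documents do not supply. Severity is low.

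**What to change.** In section 3.7.2:
1. Add sex as a fixed effect to every efficacy mixed model.
2. Add baseline cervicobrachial pain, as the randomisation stratum or as continuous NRS, to the models for outcomes other than cervicobrachial pain. The cervicobrachial pain model needs no further pain term.
3. State that the remaining baseline covariate is the outcome's own baseline value, if that is what is meant.
4. State which SD will be carried to the definitive sample-size calculation. If that trial will use the same adjusted analysis, take the SD from the adjusted model here.

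The cost is two or three sentences and 1 to 2 residual degrees of freedom out of about 45. Both variables are already collected for stratification. The article expects data collection to end in late February 2026, so the change should be recorded before the database is locked.
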